### Baseline refraction

Refraction of each USP will be conducted prior to the launch of the field visits by the skilled optometrist who will be recruited within each setting to conduct individual refraction. For example, the baseline refraction in Guangzhou will be conducted by experienced optometrists from Zhongshan Ophthalmic Center at Sun Yat-Sen University, the state key laboratory of ophthalmology. Each item of the expert prescription will be used as the “optimal spectacle prescription” (Table 1) for a given USP. The tolerance limits (Table 1) are developed from published studies [5, 25–27] and evaluated through experts’ consensus.

**Table 1 Tab1:** Criteria for optimal spectacle prescription

Component of spectacle prescription	Tolerance limits compared with baseline prescription
Spherical power	± 0.50DS
Cylindrical power	± 0.50DC
Cylindrical axis	
(if baseline cylinder power ≤ − 0.50DC) (if baseline >−0.50DC to ≤ − 1.50DC) (if baseline >−1.50DC)	± 7° ±5° ± 2°
Pupil distance	± 2 mm
Corrected visual acuity	± 0.1

DS = diopter sphere, DC = diopter cylinder

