**Fig. 1 Fig1:**
[figure not shown]
Flow chart of the study

The USPs must meet the following criteria to be eligible for the study: (1) people with refractive error profile of interest (myopia or myopia with astigmatism), and good ocular health; (2) fluent native speakers of the primary language of the district; (3) having a good memory. If the USPs meet any of the following criteria, they will not be eligible for the study: (1) having prior refractive eye surgery or had eye surgery within the last three months; (2) having manifest or intermittent strabismus, or amblyopia; (3) people with any ocular or health conditions that can cause variable spectacle prescription.

We will develop the sampling frame of all OSPs who meet our inclusion and exclusion criteria by crawling the data of Gaode Map, the leading map service App with the advantage of capturing both registered and non-registered optical shops in China. We will select the sample of OSPs with stratified and simple random sampling. Likewise, we will recruit USPs by posting part-time job announcements on campus posters and social media, like WeChat, and also through our existing USP network. The USPs will be paid for participation and reimbursed for other related expenses.

At recruitment, all USPs and their companions must sign the informed consent electronically through a web link sent by our emails. We have obtained a waiver for informed consent from the OSPs as the process may compromise the sample representation due to possible participant self-selection. We meet the criteria of consent waiver for the USP studies as stipulated by the medial ethics: (1) data analysis will only be performed at the aggregated level rather than targeting individual participants; (2) de-identification for the participating individuals and institutions will be fully implemented; and (3) services performed on USPs are not critical services where resources must be protected for the real patients [23].

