### Sample size calculation

We calculated the sample size based on the proportion of optometry accuracy, which is the primary outcome of this study. According to the previous literature [5], the proportion of optometry accuracy is 44.1% in the control group (receiving usual USP visits), and proportions in the intervention groups (receiving usual USP visits plus BVIs) are supposed to be 66.1% (when assuming the effect size of 0.22). Accounting for multiple comparisons of proportions (the proportion of optometry accuracy) for treatments vs. a control [24], the overall alpha is set to be 0.05, thus a level of significance is 0.0167 (0.05/3) by using Bonferroni adjustments. In this study, we set the power of each test at 0.9, all groups have the same sample size. And finally, a total of 456 USP visits is required, each OSP is corresponded to a USP visit. Considering 5% of dropout and/or missing data, the number of participants adds up to a total of 480 participants. The sample size required for the control group and each of the intervention group is 120 respectively. The sample size calculation was performed using PASS 15 software (NCSS, Kaysville, UT, USA).

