### Outcomes

The primary outcome is optometry accuracy, a dichotomous variable of spectacle prescription. The prescription of a specific USP visit will be considered “accurate” if all of its readings fall within the tolerance limits in Table 1 to the optimal spectacle prescription. Otherwise, they will be judged as inaccurate prescriptions.

We will also assess providers’ adherence to best practices in optometry services as the secondary outcomes, such as the percentage of guideline-recommended procedures performed. We developed the following technical process indicators based on the guideline recommendations [28]: whether practitioners perform subjective optometry, try on adjustments, check old glasses, etc., and whether the operation is standardized and completed. A technical quality assessment checklist will be developed, and the USP will complete this checklist right after each optical visit. In addition to those technical processes of optometry, we will also evaluate patient experience, cost and service time. The patient-centered eye care in optometry or ophthalmology will be assessed with a revised patient perspective patient-centeredness (PPPC-R) rating scale by USP [29, 30]. Table 2 summarizes all outcomes to be collected.

**Table 2 Tab2:** Outcomes and their definitions

Name	Definition	Nature	How it is assessed	By whom
optometry accuracy	whether it is optimally prescribed for spectacle	primary outcome	spectacle prescription	USP and companion
completion of process items	the percentage of recommended procedures performed	secondary outcome	quality checklist	USP and companion
patient experience score	whether it is patient-centered	secondary outcome	PPPC-R rating scale	USP
cost	optometry fees, prices of recommended lenses and frames	secondary outcome	data collection form	USP and companion
service time	optometry time and waiting time	secondary outcome	data collection form	USP and companion

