### Statistical analysis plan

Data will be analyzed on an intention-to-treat (ITT) basis to compare primary and secondary outcomes in the originally assigned groups. Baseline characteristics for each group will be descriptively presented using mean (standard deviation, SD) or median (interquartile range, IQR) for continuous variables depending on the distribution, and frequency (percent) for categorical variables.

Primary outcome (optometry accuracy) and secondary outcomes will be analysed using generalized linear models (GLMs). Binomial distribution and identity link function will be used for binary outcomes, Poisson distribution and identity link function will be used for count outcomes, and normal distribution and identity link function will be used for continuous outcomes. Effects (risk differences for binary and count outcomes, and mean differences for continuous outcomes) with corresponding two-sided 95% confidence intervals will be estimated. Missing data will be imputed using multiple imputation in the GLMs.

Sensitivity analysis will be performed by covariate-adjusted analysis using GLMs with baseline characteristics as covariates. Cost-effectiveness analyses will be performed, and cost-effectiveness ratios will be calculated using bootstrapping techniques. Statistical significance will be considered to be present when the P value is < 0.05. Subgroup analyses will be performed, based on the type of service (hospitals and optical shops) and types of practitioners (such as licensed vs. unlicensed practitioners). IBM SPSS (version 20) and SAS (version 9.4, SAS Institute) will be used for all statistical analyses.

Subgroup analyses will be performed, based on type of service (hospitals and optical shops) and types of practitioners (such as licensed vs. unlicensed practitioners).

We expect the number of withdrawals to be low because the intervention is delivered by the USP and the service provider will receive the intervention passively. Additionally, the intervention will be conducted over a brief period of one USP visit thus without post-visit follow-ups. All data will be entered into the REDCap system immediately after the visit. Thus, we expect to have minimum (if any) missing data. A maximum dropout and/or missing data of 5% is considered in our sample size calculation. We will analyze the data according to the ITT principle.

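### Table 1's axis-tolerance bands, part of the primary-outcome rule, are wrong as printed: on signed cylinder values the middle band is empty and the order of the limits is reversed

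*Protocol article*

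**What the plan says.** The protocol article (Methods, Outcomes) calls a prescription accurate "if all of its readings fall within the tolerance limits in Table 1 to the optimal spectacle prescription". It then adds: "Otherwise, they will be judged as inaccurate prescriptions".

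Table 1 (Methods, Baseline refraction) sets the limits relative to the expert baseline prescription. For cylinder axis it gives three conditions on the baseline cylinder: "if baseline cylinder power ≤ − 0.50DC) (if baseline >−0.50DC to ≤ − 1.50DC) (if baseline >−1.50DC". The tolerances, in the same order, are ±7°, ±5° and ±2°, so ±5° belongs to the middle condition, "if baseline >−0.50DC to ≤ − 1.50DC". Cylinder power has its own tolerance of ±0.50 DC.

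Under Participants and recruitment, the eligible USPs are "people with refractive error profile of interest (myopia or myopia with astigmatism", so a USP with no cylinder at all can be enrolled.

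**The concern.** The inequalities appear to have been written for the size of the cylinder, with minus signs then added to each limit. Putting a minus sign on a limit without reversing the inequality changes which values satisfy it. An analyst who codes Table 1 exactly as printed would apply the wrong axis limit, or two conflicting ones.

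Table 1 is the decision rule for the primary endpoint, so an error there goes straight into the accuracy rate. Under Allocation and blinding, each USP makes equal numbers of visits in all four groups. A wrong limit for one USP therefore affects every arm, and the main damage is to the level of accuracy, not to the balance between arms. The level matters in its own right, because the Control group section says the control-arm results will also serve as the survey of current service quality.

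A second, smaller question is what happens to the axis when only one of the two prescriptions being compared has a cylinder.

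**Working it through.** **The plan's own figure.** The only computed design figure is 456 visits. The inputs are 0.441 and 0.661 for accuracy, alpha 0.05/3 and power 0.90 (Sample size calculation). The unpooled two-proportion formula with a one-sided alpha gives n = (0.441×0.559 + 0.661×0.339) × (2.128 + 1.282)² / 0.22² = 0.4706 × 11.63 / 0.0484 ≈ 113.1, so 114 per arm. Then 4 × 114 = 456, and 456/0.95 = 480. No axis limit enters this, so the point does not change it.

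**Bands as printed.** Let c be the signed baseline cylinder.
- ±7° if c ≤ -0.50
- ±5° if c > -0.50 and c ≤ -1.50. Since -1.50 < -0.50, no value qualifies.
- ±2° if c > -1.50

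The first and third conditions both hold for -1.50 < c ≤ -0.50.

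**Bands by magnitude.** Let m = |c|: ±7° if m ≤ 0.50; ±5° if 0.50 < m ≤ 1.50; ±2° if m > 1.50.

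Results in quarter-dioptre steps from 0 to -3.00 DC (13 values):

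| Baseline cylinder (DC) | Number of values | Limit as printed | Limit by magnitude |
|---|---|---|---|
| 0, -0.25 | 2 | ±2° | ±7° |
| -0.50 | 1 | ±7° and ±2° | ±7° |
| -0.75, -1.00, -1.25 | 3 | ±7° and ±2° | ±5° |
| -1.50 | 1 | ±7° | ±5° |
| -1.75 to -3.00 | 6 | ±7° | ±2° |

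As printed, 4 of the 13 values meet two conflicting limits and 9 meet a single limit that differs from the magnitude reading. Only at -0.50 DC is the magnitude limit among those met. By magnitude, every value falls in exactly one band.

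**Axis on one prescription only.** Cylinder power passes within ±0.50 DC, which leaves four cases:
- Both cylinders zero: there is no axis reading, so nothing to judge.
- Baseline zero, prescribed cylinder up to 0.50 DC: power passes, but the prescribed axis has no reference.
- Baseline cylinder up to 0.50 DC, none prescribed: power passes, but there is no prescribed axis to compare.
- Either of the last two with more than 0.50 DC: power fails, so the axis does not matter.

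The gap is therefore confined to a cylinder of at most 0.50 DC on one side only.

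**How far that gap could move the rate.** The article does not give the share f of such visits, so f is an assumption. Take 44.1% accuracy among all other visits ("the proportion of optometry accuracy is 44.1% in the control group"). If all the unclassifiable visits fail, the rate is 0.441 × (1 - f). If all pass, it is 0.441 × (1 - f) + f.

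| Assumed f | All fail | All pass |
|---|---|---|
| 5% | 41.9% | 46.9% |
| 10% | 39.7% | 49.7% |
| 20% | 35.3% | 55.3% |

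These are outer bounds, because such visits would still be judged on the other components.

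**The case against.** The strongest reply is that this is a slip of notation. The tolerances are listed as 7°, 5° and 2°, and they tighten as the cylinder grows if the limits are read by size. That reading leaves no gap and no overlap, whereas the printed one leaves a band empty, which nobody intends. This stands. A reader might infer that the primary outcome cannot be scored at all; the document does not support that, because the workable reading is plain. It does not follow that the text can stay. Nothing in the article tells the analyst to use absolute values, and a threshold for the primary outcome should not depend on inference. A text-extraction fault is unlikely, since the minus sign appears on all four limits.

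On the missing axis, the reply is that a sphere-only prescription for a purely myopic USP has no axis reading and causes no difficulty. This also stands, and it limits the gap to the one-sided case shown above.

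A reader might go further and infer from the words about all readings that a prescription lacking pupil distance or corrected acuity can never fail. The article does not say so. The sentence that follows classes everything else as inaccurate. Baseline refraction makes every component a reference ("Each item of the expert prescription will be used as the"). The Statistical analysis plan section says "Missing data will be imputed using multiple imputation in the GLMs". Such a prescription could be failed, imputed or passed, and settling that is ordinary content for the full protocol or analysis plan.

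Nor do the documents support any size or direction of bias from unrecorded components, because they give no recording rates. Suppose, purely for illustration, that 55% pass sphere, cylinder and axis, that 80% of recorded distance-and-acuity pairs pass, and that the pair is recorded in 50% of control and 80% of intervention visits. Ignoring missing components then gives 0.55 × (0.84 - 0.90) = -3.3 points with no true effect, and failing them gives 0.55 × (0.64 - 0.40) = +13.2 points. The sign depends on the convention, so neither figure is a finding and neither convention is recommended here.

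**Conclusion.** The axis bands in Table 1 are wrong as written and need correcting before any visit is scored. The signed-number result is a matter of logic and rests on no assumption. Describing the printed limits as the reverse of what was meant does rest on the magnitude reading, which the order of the tolerances makes evident but the text does not state.

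The effect on the observed accuracy rate cannot be calculated, because the article does not give the distribution of baseline cylinder among the USPs. If the analysts already code by magnitude, the effect is nil apart from the small one-sided axis gap.

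**What to change.** Restate the axis rows of Table 1 on absolute baseline cylinder, after the team confirms that this matches the sources and expert consensus behind the table:
- |cyl| ≤ 0.50 DC: ±7°
- |cyl| > 0.50 to ≤ 1.50 DC: ±5°
- |cyl| > 1.50 DC: ±2°

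Add one sentence to the outcome definition: the axis criterion does not apply when the baseline or the prescribed cylinder is zero and cylinder power is within ±0.50 DC.

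The cost is a table correction and one sentence. Data collection, sample size and the analysis model do not change.

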### Outcomes

The primary outcome is optometry accuracy, a dichotomous variable of spectacle prescription. The prescription of a specific USP visit will be considered “accurate” if all of its readings fall within the tolerance limits in Table 1 to the optimal spectacle prescription. Otherwise, they will be judged as inaccurate prescriptions.

We will also assess providers’ adherence to best practices in optometry services as the secondary outcomes, such as the percentage of guideline-recommended procedures performed. We developed the following technical process indicators based on the guideline recommendations [28]: whether practitioners perform subjective optometry, try on adjustments, check old glasses, etc., and whether the operation is standardized and completed. A technical quality assessment checklist will be developed, and the USP will complete this checklist right after each optical visit. In addition to those technical processes of optometry, we will also evaluate patient experience, cost and service time. The patient-centered eye care in optometry or ophthalmology will be assessed with a revised patient perspective patient-centeredness (PPPC-R) rating scale by USP [29, 30]. Table 2 summarizes all outcomes to be collected.

**Table 2 Tab2:** Outcomes and their definitions

Name	Definition	Nature	How it is assessed	By whom
optometry accuracy	whether it is optimally prescribed for spectacle	primary outcome	spectacle prescription	USP and companion
completion of process items	the percentage of recommended procedures performed	secondary outcome	quality checklist	USP and companion
patient experience score	whether it is patient-centered	secondary outcome	PPPC-R rating scale	USP
cost	optometry fees, prices of recommended lenses and frames	secondary outcome	data collection form	USP and companion
service time	optometry time and waiting time	secondary outcome	data collection form	USP and companion

### Data collection and management

We will collect a variety of eye care quality information and other related explanatory variables. Donabedian’s classification of quality of care (structure, process and outcome) will be used for quality evaluation [31]. The quality of structure level includes: personnel qualification (whether the practitioner is qualified and professionally certified) and equipment layout (whether the facility’s hardware meet the requirements of optometry and whether its layout is appropriate), etc. This kind of information will be obtained from publicly available websites, promotional materials and USP on-site observations.

Almost all data will be collected through the USP visit to the OSPs. The USP will visit each provider along with a companion as “friend”. While the USP is under examination by the practitioner, the companion will observe the equipment environment and the optometry procedures. At the end of each visit, the USP will ask for a spectacle prescription. The USP and the companion will work together to complete the quality checklist and other data forms on the smartphone within 15 min of the end of the optometry service. We assure that all collected data will be securely stored and protected in accordance with relevant privacy regulations and guidelines.

All data collected will be entered into the Research Electronic Data Capture (REDCap) system by USP companions. REDCap is a free and powerful cloud-based tool for data collection, storage and management [32]. It will also track any changes to the data in an audit trail and be able to fully de-identify the data. REDCap has bank-level security features, and only the investigators involved in this study can access the data. All forms collected for this study, including the signed consent forms, will be stored on REDCap system safely and conveniently.

### Statistical analysis plan

Data will be analyzed on an intention-to-treat (ITT) basis to compare primary and secondary outcomes in the originally assigned groups. Baseline characteristics for each group will be descriptively presented using mean (standard deviation, SD) or median (interquartile range, IQR) for continuous variables depending on the distribution, and frequency (percent) for categorical variables.

Primary outcome (optometry accuracy) and secondary outcomes will be analysed using generalized linear models (GLMs). Binomial distribution and identity link function will be used for binary outcomes, Poisson distribution and identity link function will be used for count outcomes, and normal distribution and identity link function will be used for continuous outcomes. Effects (risk differences for binary and count outcomes, and mean differences for continuous outcomes) with corresponding two-sided 95% confidence intervals will be estimated. Missing data will be imputed using multiple imputation in the GLMs.

Sensitivity analysis will be performed by covariate-adjusted analysis using GLMs with baseline characteristics as covariates. Cost-effectiveness analyses will be performed, and cost-effectiveness ratios will be calculated using bootstrapping techniques. Statistical significance will be considered to be present when the P value is < 0.05. Subgroup analyses will be performed, based on the type of service (hospitals and optical shops) and types of practitioners (such as licensed vs. unlicensed practitioners). IBM SPSS (version 20) and SAS (version 9.4, SAS Institute) will be used for all statistical analyses.

Subgroup analyses will be performed, based on type of service (hospitals and optical shops) and types of practitioners (such as licensed vs. unlicensed practitioners).

We expect the number of withdrawals to be low because the intervention is delivered by the USP and the service provider will receive the intervention passively. Additionally, the intervention will be conducted over a brief period of one USP visit thus without post-visit follow-ups. All data will be entered into the REDCap system immediately after the visit. Thus, we expect to have minimum (if any) missing data. A maximum dropout and/or missing data of 5% is considered in our sample size calculation. We will analyze the data according to the ITT principle.

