### Allocation and blinding

The sample of OSPs will be randomly assigned to the control or the intervention groups with a 1:1:1:1 allocation. The randomization schedule will be computer-generated and stratified by service type (such as hospitals and optical shops). A stratified randomization is used to ensure that the four groups have a similar distribution in type as this characteristic may substantially affect the outcomes.

The allocation of OSPs will be conducted by a statistician otherwise not related to the research. Other than a code for each service provider and the service type, the statistician will have no other identifying information of the sampled participants.

After stratified random sampling, the allocation sequence will be generated by computer, and the randomization for each group will be initiated by the researcher. The USPs will be enrolled by the researcher and assigned randomly to the OSPs in each group. To balance confounding factor of individual USP, each USP will be assigned to four groups for equal visits.

The study subjects (OSPs) will be blinded to their allocation status as we have obtained a waiver for their informed consent. The USPs will not be blinded as they will need to implement BVIs according to the allocation status. The outcome assessors and data analysts will be blinded to reduce subjective analysis.

As no informed consent will be sought, unblinding on the side of OSPs is highly unlikely if possible at all. But if that occurs, a replacement of provider with similar characteristics will be identified for a replacement visit.

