### Control group

The control group of optical services will receive usual USP visits, while the intervention groups will receive usual USP visits plus a form of BVIs. In the usual USP visit, the customer requests to get their eyes checked for the spectacle prescription, but will otherwise make no other proactive lines. Although a schedule will be developed for each USP to visit sampled OSPs, most visits will be drop-in visits with no prior appointment unless it is a required procedure by the OSP, for example, when USPs have to register online in advance to visit the ophthalmology department of the hospital. The usual USP visit is chosen as the control, because the purpose is to investigate whether patient’s BVI will change practitioner’s behavior and thereby affect the quality of optometry service. It should also be noted that the assessment results in the control group will serve as the cross-sectional survey results of the quality of optometry service.

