## Discussion

This randomized controlled trial is designed to investigate the effect of BVI by USP on the quality of optometry service. The outcomes will include optometry accuracy, provider adherence to best practices in conducting optometry, and structural elements of the OSPs. The results of this study will not only provide valuable information on the quality of optometry service and identify a specific opportunity for quality improvement but also provide much-needed empirical evidence to aid policy-makers, education institutions and service providers on how to ensure that optical services provide quality eye care. The findings can be especially helpful for people with refractive error to obtain proper refraction and good service as BVIs can potentially be self-implemented by patients. The use of USPs in this study provides a reliable way of measuring and changing quality of the services.

Although we have waived informed consent for the OSPs, we will take strong measures to protect provider information. No service provider or practitioner identification details will be reported in publications or any other public spaces. There is also a way for USPs to prevent getting harm once their anonymity is exposed. All USPs will be intensively trained to present a letter with phone contact information from the university to explain their research roles in case of possible confrontation and also to avoid potentially harmful examination.

There are several limitations that should be considered. First, we will not be able to afford to buy spectacles due to limited budgets. So the results of the data can only reflect the provided optometry service quality, not the whole refractive error care. Second, we do not consider young children, only use adult USPs (aged 18 or up) in the study as mydriatic optometry is an invasive examination that cannot be ethically implemented in the USP study. Third, our USPs have real profiles of refractive error with various diopters, so different USPs may cause the individual difference. We will minimize the potential bias by assigning each USP to the four groups in addition to the random assignment of OSPs. Training will be provided to ensure each USP plays their roles consistently except BVI across groups.

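### The primary model leaves out service type and USP, the two factors that the allocation balances on, so its standard errors can be off in either direction

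*Protocol article*

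**What the plan says.** - **Allocation and blinding.** Randomisation is "stratified by service type (such as hospitals and optical shops"), on the ground that service type could matter substantially for the outcomes. To balance the individual USP as a confounder, "each USP will be assigned to four groups for equal visits".
- **Discussion, limitations.** "our USPs have real profiles of refractive error with various diopters, so different USPs may cause the individual difference". The stated remedy is the assignment of each USP to all four groups.
- **Statistical analysis plan.** The primary outcome is analysed with a GLM (binomial, identity link), giving risk differences with two-sided 95% intervals. No USP term, service-type term or clustered variance is named. Adjustment has a separate place: "Sensitivity analysis will be performed by covariate-adjusted analysis using GLMs with baseline characteristics as covariates". Those characteristics are not listed. Service type appears otherwise only as a subgroup factor.
- **Control group.** "the assessment results in the control group will serve as the cross-sectional survey results". The Abstract promises descriptive analysis of the survey results. No interval method is given for them.

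**The concern.** The design restricts the allocation on two factors because they are thought to matter, and the primary analysis then uses neither. An ordinary binomial GLM treats the visits as independent.

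Visits by the same USP are unlikely to be independent. All of them are judged against one baseline prescription (Baseline refraction), so any error in it is shared. USPs may have myopia with or without astigmatism (Participants and recruitment). The cylinder-axis limit in Table 1 tightens from ±7° to ±2° as the baseline cylinder grows, and every reading must fall within its limit for a prescription to count as accurate (Outcomes). The chance of passing can therefore differ between USPs for reasons unrelated to the provider.

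At stake is whether the standard errors of the three primary comparisons are right. For the single-arm survey estimate, the USP variance does not cancel as it does in a difference between arms.

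**Working it through.** **Inputs from the protocol.** "the proportion of optometry accuracy is 44.1% in the control group"; proportions in the intervention groups "are supposed to be 66.1% (when assuming the effect size of 0.22"); "thus a level of significance is 0.0167 (0.05/3) by using Bonferroni adjustments"; power 0.90 per test; 456 evaluable visits (114 per arm), 480 after 5% loss (120 per arm); one visit per provider.

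**Assumed, not in the protocol.** The ICC of accuracy within USP (ρ, 0.02 to 0.20); the number of USPs (12 or 24, so m = 10 or 5 visits per USP per arm); the service-type mix.

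**1. The plan's own figure.** Unpooled normal approximation, one-sided 0.05/3: n = (2.128 + 1.282)² × (0.441×0.559 + 0.661×0.339) / 0.22² = 11.63 × 0.4706 / 0.0484 ≈ 113.0, rounded up to 114 per arm, or 456. Then 456/0.95 = 480. The figure reproduces, but on a one-sided test. The two-sided versions tried give 528 to 580, and 114 per arm then gives about 83% power. That is a separate matter, but it means that power is not in surplus.

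**2. Arm comparisons, USP effect the same in every arm.** With equal visits per arm, the USP effect cancels from the difference but stays in the unadjusted error term. Unadjusted SE / true SE = 1/√(1−ρ).

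| ρ | SE ratio | true coverage of a nominal 95% interval |
|---|---|---|
| 0.02 | 1.010 | 95.2% |
| 0.05 | 1.026 | 95.6% |
| 0.10 | 1.054 | 96.1% |
| 0.20 | 1.118 | 97.2% |

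Power at 120 per arm, two-sided 0.0167, is 0.855 at ρ = 0 (normal deviate 1.058). The unadjusted test then has power Φ(1.058 × SE ratio):
- ρ = 0.02: Φ(1.069) = 0.857, against 0.863 with USP modelled, a gap of 0.6 points.
- ρ = 0.10: Φ(1.115) = 0.868, against 0.894, a gap of 2.6 points.

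Simulation with 12 USPs agrees: 87% against 90% at ICC 0.10, and 88% against 92% at ICC 0.17. At ICC 0.10 the unadjusted test rejects a true null 1.2% of the time against the nominal 1.67%.

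**3. Arm comparisons, intervention effect varying by USP.** Let ρᵢ be the share of variance due to USP-by-arm interaction. The true variance relative to the unadjusted one is 1 − ρ + (m−1)ρᵢ, so the direction reverses once ρᵢ > ρ/(m−1). At ρ = 0.10 and m = 10 that is 0.10/9 = 0.011; at m = 5 it is 0.10/4 = 0.025.
- ρ = 0.10, m = 10, ρᵢ = 0.02: SE ratio 1/√(0.90 + 0.18) = 0.962.
- ρ = 0.10, m = 10, ρᵢ = 0.05: SE ratio 1/√(0.90 + 0.45) = 0.861.

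Simulation at ρᵢ = 0.02 gives a true SD of 0.067, against 0.064 for the unadjusted SE and 0.060 for a USP-stratified SE. Stratifying by USP without a robust variance therefore falls further short than the unadjusted model in this case.

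**4. Service type.** With fraction q in one type and accuracy gap d, R² = q(1−q)d² / 0.2353, where 0.2353 = 0.4706/2, and the SE ratio is 1/√(1−R²). For q = 0.2, d = 0.1 it is 1.003; for q = 0.5, d = 0.3 it is 1.05.

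**5. Control-arm survey, n = 120, p = 0.441.** Independence half-width: 1.96 × √(0.441×0.559/120) = 8.9 points. Design effect: 1 + (m−1)ρ.

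| USPs | ρ | design effect | half-width needed (points) | coverage of independence interval |
|---|---|---|---|---|
| 12 | 0.05 | 1.45 | 10.7 | 90% |
| 12 | 0.10 | 1.90 | 12.2 | 85% |
| 12 | 0.20 | 2.80 | 14.9 | 76% |
| 24 | 0.05 | 1.20 | 9.7 | 93% |
| 24 | 0.10 | 1.40 | 10.5 | 90% |
| 24 | 0.20 | 1.80 | 11.9 | 86% |

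**The case against.** The strongest reply is that the design already does the important work. Balancing USPs across arms and stratifying on service type guard the comparison against confounding. With a common USP effect the type I error is not inflated, and the loss is a few power points at most. An adjusted sensitivity analysis and service-type subgroups are planned. The protocol gives no ICC, number of USPs or pass rate by refractive type, so every size above is assumed; at an ICC of 0.02 to 0.05 the intervals are only 1% to 3% too wide. All of this stands, and it keeps the point modest.

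It does not answer step 3. USPs deliver the intervention themselves, and the Brief verbal interventions section allows some latitude in the Group A wording, so an effect that varies by USP cannot be ruled out.

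Four stronger readings are tempting, and the protocol does not support them:
- A reader might infer that the effect intervals are simply too wide. That needs a USP effect common to all arms, which the protocol does not establish.
- A reader might infer that the survey result will be reported with false precision. No interval for it is stated, so the criticism applies only if an independence-based one is used.
- A reader might infer that ignoring service type also narrows the survey interval. Under proportional sampling it widens it slightly, by a factor of up to about 1.05. The undercoverage comes from USP clustering alone.
- A reader might infer that the sensitivity analysis excludes USP or service type. The covariates are unnamed, so either could be among them.

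**Conclusion.** The mismatch is real. Naming adjustment as the sensitivity analysis makes the primary model unadjusted as written, so this is a stated choice and not detail deferred to a fuller plan. Its effect on the primary comparisons is modest, and the direction is not fixed. With common USP effects, standard errors are about 1% to 12% too large (ICC 0.02 to 0.20), costing about 1 to 4 power points (ICC 0.02 to 0.17). They can be too small if the intervention effect varies by USP, from an interaction share of about 0.011 at ICC 0.10 with 12 USPs. Service type adds at most about 5% over the mixes examined.

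The possible error in a survey interval is larger, but conditional on how that interval is built. The change is worth making before analysis; nothing here invalidates the design.

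**What to change.** In the Statistical analysis plan section:
1. Make the primary estimate a risk difference adjusted for service type and USP. A stratified risk difference, or logistic regression standardised to a risk difference, would serve. A binomial identity-link model with these terms may not converge.
2. Keep the unadjusted GLM as the sensitivity analysis.
3. Beside the primary estimate, report a USP-by-arm check or a USP-clustered standard error with a small-sample correction. Step 3 of the working shows that stratification alone is not enough if the intervention effect varies by USP.
4. If intervals are reported for the control-arm survey, cluster them on USP with a small-cluster correction.
5. State the planned number of USPs and visits per USP per arm, so that the size of these effects can be judged.

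The cost is a few sentences and a little programming. Service type and USP are both known before each visit, and no extra visits are needed.
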